### Additional studies

We will measure in MORE CARE study, the difficulties to use mobile phone communications as appointment reminder tool in sub-Saharan Africa. These obstacles include:

1) Non possession of mobile phone: Possession of mobile phone will be evaluated by a yes/no question. The proportion of patients with mobiles will be compared between the three settings of the study (urban, semi-urban, and rural).

2) Obstacles on the methods and language of communication: The written communication (communication by text message) will be evaluated and will be accepted as satisfactory if the participant reads and understands the consent form. Oral communication (communication by phone call) will be accepted as satisfactory if the participant understands the questions ‘What is your name?’, ‘How old are you?’, and ‘Where do you live?’. We will compare ability to use oral and written communication. We will also compare types of communication between the three settings of the study.

3) Refusal to participate: We will measure the proportion of subjects who refuse to receive SMS or phone calls. We will compare this refusal between settings and between SMS and calls.

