### Reminder intervention

In the group receiving both SMS and phone calls (Group 4), the SMS reminder, in French or in English, will be sent between 08:00 and 12:00 AM, 72 hours before the appointment followed by a reminder phone call 48 hours before the appointment. The SMS will be sent manually. The SMS will serve as an appointment reminder and motivator. It will contain the date and the time of appointment, the location, and the name of the treating physician (Figure 3). To comply with medical confidentiality, the message will not contain any information on the health status of the child. Each text message sent will include about 300 characters including spaces. The method ‘message received’ will be used to ensure that the message was actually sent. For calls, a medical administrative assistant will phone 48 hours before the scheduled appointment, between 08:00 and 12:00 AM with communication in French or in English. A maximum of three calls attempts will be made. During the phone call, the medical secretary will remind the participant of the date and the location of his/her appointment and of the name of the treating physician. The name of the participant or the child will not be mentioned. In both SMSs and phone calls, communication is unidirectional towards the participant who cannot in return contact the medical secretary. This phone call procedure will be identical for the group receiving only phone calls (Group 3). Concerning the group receiving only the SMS (Group 2), the same procedure for sending SMS will be followed, and the SMS will be sent 48 hours before the appointment instead of 72 hours. It is important to note that, the content of communication (by SMS or by voice call) will be the same for all interventions.

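### The additional study tests written and oral ability with tasks of unequal difficulty, so its direct oral v written comparison probably favours oral communication (minor)

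*Protocol article*

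**What the plan says.** The protocol article's section on additional studies sets out to measure "the difficulties to use mobile phone communications as appointment reminder tool in sub-Saharan Africa". Its second item covers method and language of communication and fixes one pass rule per mode:

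- **Written.** Communication by text message "will be accepted as satisfactory if the participant reads and understands the consent form".
- **Oral.** "Oral communication (communication by phone call) will be accepted as satisfactory if the participant understands the questions" about the person's name, age and place of residence.

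Two analyses follow. The first is between modes: "We will compare ability to use oral and written communication". The second is between sites: "We will also compare types of communication between the three settings of the study" (urban, semi-urban and rural).

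The section on the reminder intervention shows what each channel asks of a caregiver. For the SMS: "Each text message sent will include about 300 characters including spaces". It gives date, time, location and physician. The call gives date, location and physician. The section adds that "the content of communication (by SMS or by voice call) will be the same for all interventions".

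**The concern.** A comparison of two abilities can be interpreted only if the two tests are of similar difficulty or share common items. Here the written test is a trial consent form and the oral test is three elementary personal questions. Neither resembles the reminder it stands for.

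Two kinds of misclassification follow. A caregiver who could read a short appointment message but does not understand the consent form is scored as unable to use SMS. A caregiver who understands the three questions but could not follow a date, a place and a name in French or English is scored as able to use calls. Both errors lower the written result relative to the oral one.

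What is at stake is the conclusion of this sub-study. The discussion section justifies the choice of sites partly by a better estimate of the difficulties of using phones in such settings. A reader could conclude that reading is the main barrier, and that calls are the more usable channel, when part of the gap comes from the tests.

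**Working it through.** **Is there a figure to reproduce?** The protocol gives no pass rate, expected difference or sample size for this comparison. The nearest figure is the trial's own sample size, which rests on attendance. With 0.59 v 0.84, two-sided alpha 0.05, 80% power and mean proportion 0.715:

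n = [1.96 × √(2 × 0.715 × 0.285) + 0.8416 × √(0.59 × 0.41 + 0.84 × 0.16)]² / 0.25² = (1.251 + 0.516)² / 0.0625, which is 50 per group.

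Then 50 / 0.9 = 55.6, so 56 per group and 4 × 56 = 224. This agrees with the protocol, and no input to it comes from the communication items.

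**The texts side by side.**

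| | Written / SMS | Oral / call |
|---|---|---|
| Demand in use | About 300 characters: date, time, location, physician | Date, location, physician |
| Test applied | Reads and understands the consent form | Understands three questions on name, age, residence |

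The demands in use are nearly matched; the tests are not. No item is common to both modes, so no analysis of these data can separate the effect of mode from the effect of task difficulty.

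**Direction.** If the consent form is harder than the three questions, the error favours oral communication. This is a judgement, because the form is not shown, but it is hard to see how the form could be the easier task.

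**Size: illustration only, all values assumed.** Let ability be standard normal and identical in both modes, so that the true gap is zero. Set the oral pass mark at -2 SD. The pass rate at mark m is 1 - Φ(m).

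| Written pass mark (SD) | Oral pass | Written pass | Apparent oral advantage (points) |
|---|---|---|---|
| -2.0 | 97.7% | 97.7% | 0 |
| -1.5 | 97.7% | 93.3% | 4.4 |
| -1.0 | 97.7% | 84.1% | 13.6 |
| -0.5 | 97.7% | 69.1% | 28.6 |
| 0.0 | 97.7% | 50.0% | 47.7 |

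The range runs from nothing to nearly 50 points, depending on a difficulty difference that the document does not reveal.

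**Between settings.** Within one mode the same criterion applies at every site, so the mismatch alone does not bias a comparison of written with written, or of oral with oral. The gap behaves differently. Take marks of -2 (oral) and -1 (written), for a gap of 13.6 points. In a hypothetical setting where ability in both modes is 0.5 SD lower, the marks act as -1.5 and -0.5, and the gap becomes 93.3 - 69.1 = 24.2 points. The two modes are equal in each setting, yet the gap differs. With equal marks it would be zero in both.

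**The case against.** **The item is peripheral.** It is one of three obstacles in an additional study. It is not among the primary or secondary outcomes, the stated objective or the sample size. This stands and sets the severity.

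**The tests are convenient and not absurd.** Written consent is required anyway, so using the form as a reading check adds no burden, and three basic questions are a plausible check that someone understands the language at all. This also stands for each measure taken alone. It does not rescue the direct comparison.

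**Some of the gap may be real.** Reading and listening in French or English may truly differ. A reader might infer that any observed gap is entirely an artefact, or that its size is known. The document supports neither: the illustration sets the true gap at zero by assumption and includes the case of no bias.

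**Stronger readings that the document does not support.** A reader might infer that every between-setting comparison is biased, and most where schooling is lowest. Comparisons within a mode use one criterion throughout, the protocol does not clearly plan to compare the gap across sites, and it gives no schooling or literacy figures by site. A reader might also take the written rule to demand complete mastery of the form. No threshold is stated, and how understanding is scored may be set out in the full protocol.

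**The exclusion criterion.** The participants section excludes from randomisation those who cannot communicate, read or write in English or French. This does not remove the problem: restricting the comparison to readers would hide the obstacle that the item is meant to measure.

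**Conclusion.** The concern holds for the direct oral v written contrast, and for any comparison of that gap across settings. Both pass rules and the contrast are fixed in the text, and following them confounds mode with task difficulty. The result is likely to favour oral communication. That direction rests on one assumption, that the consent form is the harder task. The size is unknown and cannot be derived from the document.

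Within-mode comparisons across settings are not biased by the mismatch. The randomised comparison, the primary outcome and the sample size are untouched. Severity: minor.

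**What to change.** **Participants still to be assessed.** Test both modes with reminder-type content of matched length and difficulty: an SMS-style text to read and a call script to hear. Use different appointment details in each mode and alternate the order, so that answers cannot be carried over from one test to the other. Score only the items that the protocol lists for both channels (date, location, physician); time is listed for the SMS alone. Apply the same pass rule to both and analyse the results as paired data within participant, for example with McNemar's test and a confidence interval for the paired difference.

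**Participants already assessed.** Report the two existing measures separately, labelled as consent-form comprehension and basic oral language, and make no direct oral v written comparison. If the items cannot be changed, the same rule should apply to the whole sample.

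**Cost.** Two items on the form and about a minute per participant, with the nurse who already collects the data. The sample would be split, possibly with few participants under the new items: the article reports recruitment as ongoing but gives the study period as January to May 2013, so the number still to come is unknown. A face-to-face test also only approximates a phone screen or a call. Dropping the direct contrast costs nothing beyond losing that result.

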#### Sample size

The primary objective is to measure the patient presence at their scheduled appointment. The calculation of the sample size will be based on the comparison of proportions of presence at appointment. The value of alpha is 0.05. The test is two-tailed. We assume that the presence at appointments using SMS as reminder and phone calls is, respectively, 59.0% and 59.6% [11]. We also assume that the difference would be 25% between the group that will receive both SMS and phone calls and the groups that will receive only an SMS or only phone calls. The minimum size of the sample required will be 50 subjects in each group for analysis by intention to treat with 80% power and a significance level of 0.05. We will exclude from analysis the participants with incomplete data. For this we assume a 10% attrition rate. Thus, we will need 224 subjects (56 in each group). WinPepi has been used to calculate the size of the sample [20].

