### Analysis plan

Data will be coded, entered, and analyzed using the Statistical Package for Social Science (SPSS) version 20.0 for Windows (SPSS, Chicago, Illinois, USA). We will describe continuous variables using means with standard deviations, and categorical variables using their frequencies and percentages. We will use the principle of ‘intention to treat’ analysis. The risk ratio will be used to measure effect of interventions on proportion of presence at medicals appointments and will be expressed with 95% confidence interval. The *t*-test will be used to compare quantitative variables, and the chi-square test will be used to compare qualitative variables. A *P* value less than 0.05 will be considered statistically significant. WinPepi will be used to measure the interaction between SMS and call in the group receiving both call back methods of appointment.

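### Oral and written ability are rated in the same participants, but the only categorical test the plan names is the chi-square test, and no paired test is given

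*Protocol article*

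**What the plan says.** The Additional studies section of the protocol article describes a sub-study of obstacles to mobile phone reminders. Written communication counts as satisfactory if the participant can read and understand the consent form. Oral communication counts as satisfactory if the participant understands three simple spoken questions. Both ratings are yes/no and both are made on the participant. The section then says: "We will compare ability to use oral and written communication". On refusal it says: "We will compare this refusal between settings and between SMS and calls". It also compares phone possession and types of communication across the urban, semi-urban and rural settings.

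The section names no test. The Analysis plan gives a general rule, that "the chi-square test will be used to compare qualitative variables". Table 1 likewise lists only the chi-square test for comparing percentages. No paired method for binary data appears anywhere in the article.

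**The concern.** Comparing oral with written ability in one set of people is a paired comparison. The information lies in the discordant people, those satisfactory on one channel and not on the other. An ordinary chi-square test sets the two percentages side by side as if they came from two separate groups. It counts each person twice and leaves out the within-person covariance.

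The direction of the error depends on that covariance. Someone who can read French or English will usually understand it when spoken, so a positive correlation is likely, although the article does not say so. The unpaired test is then conservative: its P value is too large, and a true gap between the channels may be reported as no difference. With a negative correlation it would err the other way.

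**Working it through.** **The plan's own figure.** The sub-study has no sample size of its own. The main calculation reproduces. Inputs from Sample size: two-sided alpha 0.05, 80% power, 59.0% (SMS) or 59.6% (call), and a difference of 25 points.

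n = [1.96·√(2p̄q̄) + 0.8416·√(p₁q₁ + p₂q₂)]² / (p₂ − p₁)²

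For 0.59 v 0.84: p̄ = 0.715, so n = (1.96 × 0.6384 + 0.8416 × 0.6134)² / 0.0625 = 50. For 0.596 v 0.846 the result is also 50. Then 50/0.9 rounds up to 56, and 4 × 56 = 224. The present point changes none of this.

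**Formulas for the paired comparison.** Let p_w and p_o be the proportions satisfactory in writing and orally, d = p_o − p_w, and p₁₀ and p₀₁ the proportions satisfactory in writing only and orally only.

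- Unpaired SE = √[(p_w q_w + p_o q_o)/N]
- Paired SE = √[(p₁₀ + p₀₁ − d²)/N]
- McNemar z = dN / √[N(p₁₀ + p₀₁)]

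The article gives no ability rates, no correlation and no number screened. Everything below is therefore assumed. N = 224 is used only as a convenient size.

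**Illustration 1: nested abilities.** Written 190/224, oral 200/224, all readers also understand speech, so the discordant counts are 10 (oral only) and 0.

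- Chi-square: pooled proportion 390/448 = 0.8705; z = 0.0446/√(2 × 0.8705 × 0.1295/224) = 0.0446/0.0317 = 1.41; P = 0.16.
- Exact McNemar: 2 × (1/2)¹⁰ = 0.002.

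**Illustration 2: written 85%, oral 90%, correlation varied.** Worked line for correlation 0.4: covariance = 0.4 × √(0.85 × 0.15 × 0.90 × 0.10) = 0.0428; proportion satisfactory on both = 0.765 + 0.0428 = 0.8078; p₁₀ = 0.0422, p₀₁ = 0.0922; paired SE = √[(0.1344 − 0.0025)/224] = 0.0243.

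| Correlation | Unpaired SE | Paired SE | Chi-square P | McNemar P |
|---|---|---|---|---|
| 0 | 0.0312 | 0.0312 | 0.11 | 0.11 |
| 0.2 | 0.0312 | 0.0279 | 0.11 | 0.075 |
| 0.4 | 0.0312 | 0.0243 | 0.11 | 0.041 |
| 0.6 | 0.0312 | 0.0199 | 0.11 | 0.013 |

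**Illustration 3: fixed margins, discordant split varied.** Written 206/224, oral 215/224; chi-square P = 0.074 throughout.

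| Oral only v written only | Exact McNemar P | Unpaired SE / paired SE |
|---|---|---|
| 9 v 0 | 0.004 | 1.71 |
| 12 v 3 | 0.035 | 1.31 |
| 15 v 6 | 0.078 | 1.10 |
| 18 v 9 | 0.12 | 0.97 |

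**Actual size of the unpaired test.** With equal margins the true variance is (1 − ρ) times the one assumed, so a nominal 5% test has size 2[1 − Φ(1.96/√(1 − ρ))]. This is 2.8%, 1.1% and 0.2% at ρ = 0.2, 0.4 and 0.6, and 6.2% at ρ = −0.1.

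**The case against.** Several objections have force.

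- *The people randomised were already screened for these abilities.* Under Participants, those unable to communicate, read or write in English or French are excluded from randomisation. The 224 should show almost no discordance, so figures built on 224 do not forecast this trial. This stands. The natural denominator is everyone screened, a number the article does not give. The pairing problem is the same at any N.
- *The conclusion need not change.* This also stands: at correlation 0.2 in the second illustration, and at 15 v 6 or 18 v 9 in the third, both tests fall on the same side of 0.05.
- *Refusal may not be paired.* A reader might infer that each person can refuse either channel, because consent precedes allocation under Randomization. The article does not say that everyone is asked about both, so an error in the refusal comparison is not established.
- *No interval is at stake.* A reader might infer that the plan will publish confidence intervals that are too wide. The Analysis plan promises an interval only for the attendance risk ratio. What is affected here is a P value.
- *The sub-study is mainly about settings.* Most of its listed comparisons are between the three settings, where chi-square is suitable. Oral versus written is one comparison among several.
- *The test could be left to a fuller document, and McNemar's statistic is itself a chi-square.* This carries less weight. The article does state a rule, it covers all qualitative variables, and nothing signals a paired version. An analysis plan that follows it would repeat the error.

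**Conclusion.** The point holds for oral versus written ability. The two ratings are made on the same participant, the only categorical test named is chi-square, and that test is correct only at zero within-person correlation. Under the assumed rates, its standard error is about 1.1 to 1.6 times too large at correlations of 0.2 to 0.6. In the nested illustration P is 0.16 where the paired test gives 0.002. These sizes rest on assumed rates, an assumed positive correlation and an illustrative N. The direction follows from the design once the correlation is positive.

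For SMS versus call refusal the point is conditional on each person being asked about both channels. Confidence is high that oral and written ratings are paired and that no paired test is named, and lower on how much the result would change. Severity is minor: the comparison is ancillary, the likely error is conservative, and the randomised attendance comparison and the sample size are untouched.

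**What to change.** Add one sentence to the Analysis plan. Oral versus written ability will be compared by McNemar's test (exact when discordant pairs are few), with a paired confidence interval for the difference, among all people screened and not only those randomised. Use the same method for SMS versus call refusal if each person is asked about both channels, and state whether they are. Keep the chi-square test for comparisons between the three settings.

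The cost is the sentence, plus keeping both ability ratings for screened people who are then excluded, which the sub-study needs in any case. McNemar's test is available in the named software. No extra participants or visits are required.

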### Ethical considerations

The trial was approved by the Faculty of Medicine and Biomedical Sciences, University of Yaoundé 1. The trial was approved by National Research Ethics Committee for Human Health of Cameroon (Ethical approval N° 2013/03/232/L/CNERSH/SP). The study will be conducted in accordance with Declaration of Helsinki [22]. Prior to enrollment, all eligible participants will provide written informed consent.

## Discussion

Some studies investigating the use of mobile text message and phone calls to improve adherence to medicals appointments showed various results [10-13,15-18]. Unlike those studies, our MORE CARE trial will measure a possible synergic interaction of combining text message and phone call. Globally, the use of SMS and phone call reminders in adult studies improve appointment attendance. Improving adherence to scheduled medical visits can play a key role in better management of chronic diseases in resource limited setting. Findings of this trial can be generalized to other chronic diseases. The MORE CARE trial therefore offers a significant an opportunity to promote health in low-income countries using existing mobile cellular technology.

The choice of a multicenter study involving three regions different in their socioeconomic and demographic characteristics, and urban, semi-urban and rural settings will allow us to have a better estimation of the difficulties in using mobile phone technology in resource limited setting; this will provide supplementary information and complete the findings of Mbuagbaw *et al*. who conducted a singled-center randomized controlled trial on mobile phone text messaging versus usual care for improving adherence to highly active ART in Cameroon [23].

A major potential risk of use of mobile phone would be an accidental disclosure of HIV status of children. This potential effect will be explained clearly to the participant. This is why we choose not to mention the status of children during call and in text messages. In similar trial in Uganda, there was no issue of privacy and confidentiality [14]. In a trial in Cameroon, using text message for improving adherence to ART, one female withdrew from the study because she felt it had compromised her confidentiality [23]. In developing countries, fear of non-respect of personal data privacy can also limit the use of text message reminders [24].

Compared to SMS, which is not interactive, a phone call is a better channel for message delivery to patients or their close relatives. On the other hand, unlike a phone call, in using SMS, if the recipient is not immediately reachable when the message is sent, he/she can read the text message afterwards. In addition, in Africa, some barriers like timing of messages, mobile network fluctuations, and mobile phone turnover can reduce the potential use of mobile phone technology to improve adherence to treatment [24]. Other barriers include language impediments and lack of financial incentive.

Some factors associated with non-adherence to ART in the adult population in Cameroon can influence presence at appointment: high monthly income, binge drinking, drug and tobacco use, lack of family support for adherence, potential for experiencing discrimination and stigma, switching regimen, increased duration on medication, cost of care, increased distance from clinic, large hospital size, and no task shifting from physician to other staff [25]. In some previous studies, the sending of SMS was the less financial cost method compared to voice phone call [17]. The use of mobile phone reminder in this trial can reduce impact of some correlates of nonattendance to medical appointments in Cameroon.

Finally, the study will possibly contribute to increasing evidence of the usefulness of mobile phone technology for promoting health in low- to middle-income countries like Cameroon [26].

